## PROCEDURES/METHODOLOGIES

The intensive motor skill training consists of an adaptation of HABIT-ILE. This intervention, which we developed initially for children with CP over 6 years old, is carried out in a camp setting, with structured tasks of increasing motor difficulty and functional activities that require the use of both hands whilst sustaining postural activity or activities of the lower extremities. The therapy, using games and functional activities, is delivered in a child-

friendly environment. The tasks are chosen according to individualized functional goals previously defined by the parents (e.g. drinking or sitting autonomously, playing without help, etc.).

Although the basic principles of HABIT-ILE will be followed (Bleyenheuft & Gordon, 2014), the toys, tasks and activities will be adapted to induce spontaneously bimanual use. The duration of activities as well as lower extremities/postural associations will also be adapted to each infant depending on his/her functional objectives and personal characteristics (motor and attentional level, for instance). Eight to ten infants will undergo rehabilitation during one intensive session of 2 weeks; each infant will have a full-time therapist dedicated to his/her treatment. The follow-up of the guidelines and the fidelity to the treatment principles will be ensured through the supervision of all interventions by the post-doctoral coordinator dedicated to the project. As 50 to 60 hours of intensive therapy are needed to induce long-term motor changes (Brandão et al., 2018; Sakzewski et al., 2015), this project, in agreement with the usual motor activity time (Van Cauwenberghe et al., 2011) and the need for infants to rest, includes 5 hours per day of therapy with the same therapist for a total of 50 hours. HABIT-ILE for infants has been tested in a pilot study (illustrations in section “pilot results”) which has confirmed previous evidence that this therapy intensity is both practically feasible and efficient for children that age (Taub et al., 2004).

The time-equivalent control period consists of the child’s usual activity, including nursery, usual rehabilitation, etc. Both the content of this activity (notebook) and the time of activity (wearable sensors used in both groups to monitor the amount of movements) will be documented. This approach enables the comparison of the structured aspect of motor activities in therapy compared and “spontaneous activities” to be carried out.

The MRI procedure will consist in nap or night MRIs. Infants will undergo a standardized gradual adaptation program to make them accustomed to the very specific conditions of the MRI environment, including the wearing of ear-plugs previous to the scanning nights, bottle feeding just prior to the MRI scan, a careful examination of each infant’s sleep routines, etc (Dean et al., 2014).

## EVALUATION CRITERIA

**Primary imaging outcomes** (CST integrity measured with DTI, microstructures and myelination maps) will be measured at T0, T0+15 days and T0+90 days. We will use the classical DTI indicators of fractional anisotropy (index of fiber coherence and integrity), radial diffusivity (index of axon diameter and myelination), axial diffusivity, and mean diffusivity. These measures have been successfully used to demonstrate structural modifications of the CST, and provide an estimation of the fiber quality (Krägeloh-Mann & Cans, 2009). In addition we will use new advanced mathematical models which provide the opportunity to separately characterize fascicles of axons in areas of the brain where multiple white matter tracts intersect, allowing thus to better identify fibers of the CST from other crossing tracts, quantify CST projections, localize brain inflammation and detect axonal loss (Scheck et al., 2015). Tractography will be used to highlight potential macroscopic changes in CST organization (Bleyenheuft, Dricot, et al., 2015). Myelin maps will be used to assess global changes in myelination (Ganzetti et al., 2014). In addition, morphometric analysis (cortical thickness, cortical folding and sulcal depth) based on conventional T1 imaging will be used to investigate potential changes in grey matter (Remer et al., 2017). Resting state fMRI will also be used to explore the potential changes in brain’s functional organization and connectivity (Wen et al., 2019). All MRI data will be analyzed by an MRI specialist unaware of the treatment allocation. Although some of these measures have already been performed in infants, notably in premature babies (Deoni et al., 2015; Eaton-Rosen et al., 2017; Remer et al., 2017; Wen et al., 2019), they have never documented potential neuroplastic changes before and after an intensive intervention.

**Clinical outcomes include functional changes at the 3 levels of the International Classification of Functioning, Disability and Health (ICF):** i. the **body level**, assessment of movement control, both movement pattern and quality, through **biomechanics** (i.e. electromyographic and kinematic short assessments using an optoelectric motion capture system in a task designed for infants (Ransburg et al., 2017)), and assessment of sensory processing through the Sensory Profile 2 questionnaire (Dunn & Westman, 1997; Provost & Oetter, 1994); ii. the **activity level** (gross motor function using the Gross Motor Function Measure (GMFM-66) (Russell et al., 2010), and manual ability using the Mini-Assisting Hand Assessment (mini-AHA) (Greaves et al., 2013); and, iii.

functional skills and **participation level** (PEDI-CAT (Kramer et al., 2016) , YC-PEM (Khetani et al., 2015) and the Canadian Occupational Performance Measure (Dedding et al., 2004)). All physical assessments will be videotaped and blindly scored. These clinical assessments will allow us to document whether functional abilities of the infants are improved after intervention, their nature and extent, and their correlation with neuroplastic changes. Although the number of assessments might seem quite high for children of this age, the estimated time to carry out the full assessment is less than 2 hours for the functional assessment, 30 minutes for MRI and 30 minutes for 3D movement analysis. The primary clinical outcome will be the mini-AHA. The other tests spanning the 3 ICF domains will be used as secondary clinical outcomes.

## STATISTICAL ANALYSIS

No DTI pre-post intervention analyses in infants have been published so far. However, since CST integrity measured with DTI is highly correlated with manual ability (Bleyenheuft et al., 2007), we performed a sample size calculation based on the AHA score of the pilot study performed in 10 infants with unilateral CP (see “pilot data”). A mean improvement of 8,2 AHA units (standard deviation=5.9 AHA units) after the intensive therapy was reported. Thus, our hypothesis is an incremental improvement of 1 SD between the HABIT-ILE group and the control group (between group difference =7,2, SD=5,9). With  $\alpha=0.05$  and a  $1-\beta=0.9$ , a sample size of **15 participants per group is required**. Considering potential drop-outs and data loss in MRI, **24 participants will be included in each group**. Neuroplastic changes and secondary outcomes will be compared between groups using analysis of variance (ANOVA). Non-parametric methods will be performed whenever ANOVA assumptions are not met. Time-onset influence will be tested at the 4th assessment using an ANOVA.

Separate generalized linear models (GLM) will be estimated for the CST and whole-brain WM (ICTEAM models) to infer the correlations between  $\mu S$  integrity at baseline/after intervention and the MskL outcomes (bimanual SAT). Finally, an overall GLM will be estimated to combine CST and whole-brain  $\mu S$  integrity. The *R* software will also be used for bimanual MskL curves modelling.

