## METHODS AND STUDY DESIGN

A randomized trial (RCT) is at the core of Grand Challenge 2, involving **48 infants** with CP between 6 and 18 months. Inclusion criteria will include: being diagnosed or considered at high risk of unilateral (RCT1) cerebral palsy, 6 to 18 months inclusive and ability to complete testing according to the age. Exclusion criteria will include epilepsy, botulinum toxin injections or orthopedic surgery within the past six months or during the study period, as well as severe visual and cognitive impairments preventing the child from being interested in simple games.

A pair-matched randomization will be used. Group allocation to either HABIT-ILE or a control condition will be randomly determined within each pair. As depicted in Figure 3, the HABIT-ILE group (n=24) will receive 50 hours of treatment over 2 weeks (5 h/day, 5 days/week) whereas the control group (unilateral n=24) will follow their usual activities for 2 weeks (nursery, ongoing therapy, generally a few hours of neurodevelopmental therapy per week, etc.). Usual activities have been chosen as control intervention since spontaneous activity of infants is oriented towards the discovery of their environment with motor activities in a nursery reaching around 5 hours per day. The between-group comparisons will be carried out between T0 and T+15 and between T0 and T+90. Participants in the control group will be offered HABIT-ILE training after assessment period 3. A supplementary assessment of this group at T0+180d will allow us to investigate the influence of the onset of therapy time and persistence of the therapeutic effects on the long term.

Each assessment will comprise clinical outcomes, biomechanical assessment, and neuroimaging outcomes (traditional and multi-shell HARDI DW-MRI).

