1. superior, clinically meaningful, gains on both activity limitation (1ary clinical outcome) and other clinical outcomes in the three domains of the ICF (2ary clinical outcomes) **(HP3.0)**
2. changes in white matter microstructure (WM-μS) integrity of the CST and cortico-cortical connections (1ary imaging outcomes) **(HP3.1)**
3. changes in WM-μS integrity that correlate with mid-term changes in clinical outcomes (follow-up) **(HP3.2)**
4. functional gains predicted by baseline WM-μS integrity of the CST **(HP3.3)**
5. functional gains predicted by baseline aptitude to achieve bimanual motor skill learning (MskL) **(HP3.4)**

We will systematically explore whether, in chronic hemiparetic stroke patients, the HABIT-ILE intervention induces superior, clinically meaningful, gains compared to conventional rehabilitation **(HP3.0)**. The core experimental design of this cross-over randomized clinical trial (RCT) will be identical to that of Grand Challenge 2. *Of crucial importance will be the comparison between patient’s subgroups training either with HABIT-ILE or with in-time-equivalent control period including daily activities and usual rehabilitation. Importantly, two common behavioral assessments will be used in CP children and adult stroke patients: AHA and COPM.*

Applying ICTEAM mathematical models, we will compute WM-μS integrity tools to test whether WM-μS integrity and lesions to specific brain structures impact functional changes **(HP3.1)**. Using these ICTEAM advanced mathematical models, the WM-μS integrity of the CST (the key descending motor tract) and that of the whole brain will be explored with an unprecedented level of precision and compared to “classical” approaches using tractography with DTI measures as FA, RD and MD. Both the behavioral and MRI acquisitions will be performed pre- and post-intervention/control period and repeated at follow up (3 months), to explore

whether WM- $\mu$ S integrity evolution correlates with mid-term clinical outcomes and to help refine ICTEAM models (HP3.2).

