## STATISTICAL ANALYSIS

Since HABIT-ILE has never been applied in adult stroke patients, we based our sample size on motor changes observed previously in in school-aged children with brain lesions. We performed a sample size calculation based on the UL changes observed in the assisting hand assessment (AHA) [ref Bleyenheuft et al, 2015]; we expect a similar effect size here. Thus, our hypothesis is an incremental improvement of 1 SD between the HABIT-ILE group and the control group (between group difference=6, SD=5). With  $\alpha=0.05$  and a  $1-\beta=0.9$ , a sample size of 16 participants per group is required. Considering potential drop-outs and data loss in MRI, **24 participants will be included in each group**. Neuroplastic changes and secondary outcomes will be compared

759 between groups using analysis of covariance (ANCOVA) to adjust for baseline measurement. Non-parametric  
760 methods will be performed whenever ANCOVA assumptions are not met.

761 The *R* software will be used under the supervision of statisticians for pre-specified stat. analyses as we did  
762 before [46,47, 57]. Separated generalized linear models (GLM) will be estimated for the CST and whole-brain  
763 WM (ICTEAM models) to infer the correlations between  $\mu$ S integrity at baseline/after intervention and the  
764 MSkL outcomes (bimanual SAT). Finally, an overall GLM will be estimated to combine CST and whole-brain  $\mu$ S  
765 integrity. The *R* software will also be used for bimanual MskL curves modelling.

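### For imaging and secondary outcomes the infant trial fixes ANOVA with no baseline covariate where the adult trial fixes ANCOVA; the same adjustment is nearly free and modestly improves precision

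*Protocol*

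**What the plan says.** The infant section (Grand Challenge 2, Statistical analysis) states: "Neuroplastic changes and secondary outcomes will be compared between groups using analysis of variance (ANOVA"). Non-parametric methods are the fallback, and no covariate is mentioned. Neuroplastic change in white matter is the primary imaging outcome of this trial (Grand Challenge 2, Research hypotheses and Evaluation criteria).

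The parallel sentence in the adult section (Grand Challenge 3, Statistical analysis) covers the same two categories but compares them "between groups using analysis of covariance (ANCOVA) to adjust for baseline measurement". The Grand Challenge 3 hypotheses section adds: "The core experimental design of this cross-over randomized clinical trial (RCT) will be identical to that of Grand Challenge 2".

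Infant baseline data are available. The imaging outcomes "will be measured at T0, T0+15 days and T0+90 days", and every assessment also includes the clinical outcomes. On what is compared, Grand Challenge 2, Methods and study design, says: "The between-group comparisons will be carried out between T0 and T+15 and between T0 and T+90". The same section allocates infants within matched pairs. It does not name the matching variables, and the statistical section does not mention the pairs.

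**The concern.** The protocol itself fixes the method here, so this is not a detail left open for an analysis plan. An analysis plan that followed the text would inherit an ANOVA without baseline adjustment, although the adjustment is available at no extra data collection and is specified for the adult trial.

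What is at stake is precision, mainly for the imaging outcomes. These face expected scan loss: the section on project risks expects repeated infant MRI to succeed in at least 70% of infants. The sample size was not derived from imaging data, because the protocol says that no pre-post DTI analyses in infants had been published.

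**Working it through.** **The plan's own figure.** The infant sample size uses "between group difference =7,2, SD=5,9", with alpha 0.05 and power 0.90. Two-sided normal approximation: n = 2 × (1.960 + 1.282)² × (5.9/7.2)² = 2 × 10.51 × 0.6715 = 14.1, rounded up to 15. This matches "15 participants per group is required". The noncentral t distribution gives 16, with 89.7% power at 15.

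**What the SD measures.** The 5.9 comes from this sentence: "A mean improvement of 8,2 AHA units (standard deviation=5.9 AHA units) after the intensive therapy was reported". It therefore reads as the SD of a change. This and the comparison windows counted from T0 point to change from T0 as the analysed response, though the ANOVA sentence does not say so.

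**Variance under each analysis.** Let s² be the variance of the outcome, equal at both times, and rho the correlation between baseline and follow-up.
- ANOVA on change: 2s²(1 − rho)
- ANOVA on follow-up values only: s²
- ANCOVA with the T0 value: s²(1 − rho²)

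The ratio of ANCOVA to change-score ANOVA is (1 − rho²)/(2(1 − rho)) = (1 + rho)/2. The ratio of ANCOVA to follow-up-only ANOVA is 1 − rho².

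**Inputs for power.** The documents give no rho, so 0.5 to 0.9 is assumed. Usable scans: 0.70 × 24 = 16.8, about 17 per group. No imaging effect size is given, so the effect is assumed to be one SD of change. Power is two-sided at 0.05 from the noncentral t, for two independent groups, with one degree of freedom removed for the covariate.

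| rho | ANCOVA / change | Saving | ANCOVA / follow-up only | Saving | Power, ANCOVA | Power, follow-up only |
|---|---|---|---|---|---|---|
| 0.5 | 0.75 | 25% | 0.75 | 25% | 90.3% | 80.7% |
| 0.7 | 0.85 | 15% | 0.51 | 49% | 86.5% | 59.1% |
| 0.8 | 0.90 | 10% | 0.36 | 64% | 84.5% | 43.2% |
| 0.9 | 0.95 | 5% | 0.19 | 81% | 82.6% | 24.4% |

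Power for change-score ANOVA is 80.7% in every row, because the effect is expressed in SDs of change.

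**Small-sample cost.** Estimating the covariate slope inflates the ANCOVA variance by about 1 + 1/(2n − 4). At n = 17 this is 1 + 1/30 = 1.033, so the ratios to change-score ANOVA become 0.775, 0.878, 0.930 and 0.982. At rho 0.9 the net saving is about 1.3%, 1.8% and 2.8% for 15, 17 and 24 per group. The power column does not include this factor and is slightly favourable to ANCOVA.

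**The case against.** The strongest reply is that the loss is small. If the ANOVA is on change, baseline is already used by subtraction. The comparison is then unbiased under randomisation and targets the same effect as ANCOVA, and at a high correlation almost nothing is gained. The figure of 17 scans is also a floor. All of this stands, and it limits the point to a modest gain in efficiency.

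A reader might infer more than the documents support:

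- **That 24 infants per group are worth only about 9.** This follows from 24 × 0.36 = 8.6, which needs the follow-up-only reading and rho = 0.8. The comparison windows and the reference to neuroplastic changes make that reading the less likely one.
- **That the primary clinical outcome is affected.** The mini-AHA is not named in the infant ANOVA sentence, and the ad-AHA is not named in the adult ANCOVA sentence. No mismatch is documented for either. For the planned difference of 7.2 with 24 per group, power on change is 98.5% without adjustment and 98.9–99.8% with it.
- **That regression to the mean biases a change-score comparison.** It is equal in expectation in both randomised arms.
- **That Grand Challenge 4 is undermined.** Its hypotheses concern remodelling from baseline and how response relates to baseline markers. None sets one trial's between-group estimate against the other's.
- **That the infant groups are unprotected against baseline imbalance.** Pair matching may help, but the matching variables are not stated, so the protection cannot be quantified.

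The claim of an identical core design should not be pressed too far either: allocation is by matched pairs in infants and by minimisation in adults. That difference does not explain dropping the baseline covariate.

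**Conclusion.** The point holds for the infant trial's neuroplastic (primary imaging) and secondary outcomes. The protocol fixes the less efficient method there, uses the better one for the same categories in the adult trial, and gives no reason.

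On the likelier change-from-T0 reading, the cost is about 5–25% of residual variance for rho from 0.9 down to 0.5, with little net gain near 0.9. With about 17 scans per group and an effect of one SD of change, this means roughly 81% power against 83–90%. On the follow-up-only reading the cost is 25–81% of variance. These sizes rest on the assumed correlation, equal variances at both times, the assumed effect and the 70% scan success rate, and they ignore the pairing. The direction does not depend on the reading: over this range ANCOVA has the smaller variance under both. This is a worthwhile, inexpensive correction and not a flaw that threatens the trial.

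**What to change.** In Grand Challenge 2, Statistical analysis, replace ANOVA by ANCOVA with the T0 value of the outcome as covariate for the between-group comparisons of neuroplastic changes and secondary outcomes, as the adult section does. Make the sentence on non-parametric methods refer to the ANCOVA assumptions.

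Reflect the matched pairs in the same model. A random pair effect is preferable to a fixed one where scans are lost. With fixed pairs, only pairs with both scans inform the comparison, which at 70% success and independent losses is 0.70 × 0.70 × 24 = 11.8, about 12 of 24 pairs. Age at T0 may be added as a covariate but is optional.

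The cost is a small change of text and one degree of freedom for the T0 covariate, plus whatever the pair term uses. It needs no new data, visits or patients.

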During the two proposed randomized controlled trials (RCTs), high-quality, quantitative data will be collected in both CP infants and stroke adults before and after intensive neurorehabilitation with HABIT-ILE. First, clinical scores will be collected following well-established and validated assessments. Second, biomechanical data will be acquired. In the CP study, it will consist of optoelectronic motion capture measurements. In the chronic stroke study, it will be obtained on the REAplan® bimanual neurorehabilitation robot installed at CHU UCL Namur (Mont-Godinne). Third, neuroimaging will be performed, for both populations, on the new 3-Tesla GE MRI scanner installed at Cliniques Universitaires UCL Saint-Luc in the fall of 2019. Conventional MRI such as T1 and T2 will be supplemented with advanced DW-MRI leveraging the new scanner's capabilities. A number of mathematical models, from traditional DTI to our latest developments, will be fitted to the DW-MRI data to produce whole-brain maps of WM microstructural indices in complement to global WM connectivity maps.

This project is a unique opportunity to investigate the difference induced by intensive neurorehabilitation in the  $\mu S$  of the brain and to understand the specificity of changes in mature and immature brain to better target the components needed to induce neuroplasticity and functional recovery in each. Our efforts will also lead to the creation of an outstanding data set of DW-MRI signals and the related evaluations of motor capabilities, for both adults and children with acquired brain damage leading to life-long motor impairments. It will also set the foundation of a multidisciplinary platform for the development of neuroimaging tools. The global outreach of this project will therefore extend far beyond the walls of our research facilities at UCLouvain.

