### **A multi-modal approach predicts and explains motor recovery (HP1.2)**

The acquisition of data from multiple modalities lies at the core of this project. Patients undergoing neurorehabilitation will be evaluated using well-established and quantitative clinical scales. They will also be subject to biomechanical recordings either through a camera motion capture system (WP 2) or using a specifically-designed neurorehabilitation robot (WP 3). Each patient’s trajectory will therefore be thoroughly documented with a massive amount of data which our team at ICTEAM will mine using the latest advances in data analysis. Indices pertaining to different feature spaces (clinical scores, biomechanical measurements and neuroimaging) collected before treatment will complement each other to provide biomarkers able to quantify patients’ motor and function recovery.

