We propose an evaluation of the effects of HABIT-ILE in 6-18 month old infants based on a comprehensive functional, neurological and biomechanical assessment. HABIT-ILE is an intervention based on motor skill learning principles which focuses on the bimanual use associated to postural and/or gross motor stimulation (Bleyenheuft & Gordon, 2014). Its efficiency has already been demonstrated for both upper and lower extremities in children with unilateral (Bleyenheuft, Arnould, et al., 2015) and bilateral CP (Bleyenheuft et al., 2017) between 6 and 18 years old. **We aim to show for the first time that HABIT-ILE prevents secondary motor damage in 6-18 month old infants by treating one of its causes.**

We aim to demonstrate the effectiveness of HABIT-ILE in preventing secondary damage in CP children. More specifically, we will test the following research hypotheses. In infants with unilateral CP:

1. the HABIT-ILE intervention induces superior, clinically meaningful gains on both activity limitations (primary functional outcome) and impairments (**HP2.0**)
2. The HABIT-ILE intervention induces an increase in myelination evidenced by a change in white matter microstructure integrity of the CST and cortico-cortical connections as measured from DW-MRI (primary imaging outcome), a decrease in brain inflammation, an increase in CST projections to the spinal cord, and prevents CST reorganization in the affected hemi-cortex of infants with unilateral CP (**HP2.1**)
3. the changes in WM- $\mu$ S integrity correlate with mid-term changes in clinical outcomes (follow-up) (**HP2.2**)
4. the functional gains will be predicted by baseline WM- $\mu$ S integrity (**HP2.3**)

5. therapy onset in the course of infants development might influence long-term neuroplastic and functional changes, earlier onset might induce larger changes (HP2.4)

[figure not shown]

Figure 3: Design of the randomized controlled trial for a population of infants with cerebral palsy.

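### The infant trial's association model uses the stroke trial's robot outcome, which infants do not have; the adult model can be fitted but does not match HP3.3 or HP3.4

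*Protocol*

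**What the plan says.** **Infants, Grand Challenge 2, Statistical analysis.** Group comparisons use ANOVA. Association is then addressed by separate GLMs for the corticospinal tract (CST) and whole-brain white matter, relating microstructural "integrity at baseline/after intervention and the MskL outcomes (bimanual SAT", followed by an overall GLM that combines the two and by modelling of bimanual MskL curves in R.

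**What infants are assessed on.** The Introduction says of biomechanical data: "In the CP study, it will consist of optoelectronic motion capture measurements". HP1.2 divides the methods the same way: "either through a camera motion capture system (WP 2) or using a specifically-designed neurorehabilitation robot (WP 3". The Grand Challenge 2 Evaluation criteria specify "electromyographic and kinematic short assessments using an optoelectric motion capture system in a task designed for infants", together with Sensory Profile 2, GMFM-66, mini-AHA, PEDI-CAT, YC-PEM and COPM. They add: "The primary clinical outcome will be the mini-AHA".

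**Infant hypotheses.** HP2.2 links change in microstructure to mid-term clinical change. HP2.3 reads "the functional gains will be predicted by baseline" microstructural integrity.

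**Adults, Grand Challenge 3.** The statistical section repeats the GLM paragraph almost unchanged, again with "MSkL outcomes (bimanual SAT" as the behavioural variable. HP3.2 and HP3.3 parallel HP2.2 and HP2.3. HP3.4 is "functional gains predicted by baseline aptitude to achieve bimanual motor skill learning (MskL".

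**The concern.** The infant paragraph reads as stroke-trial text carried over. If it is followed literally, the analyst has no data for the behavioural side of the model. Someone must then choose another outcome, and the plan lists many clinical scales alongside at least four families of diffusion model (DTI, NODDI, DIAMOND, Microstructure Fingerprinting). A choice made after the data are seen would weaken any brain-behaviour result.

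The adult fault is different. The variable is collected, but it is not the quantity that HP3.3 and HP3.4 ask about. The stated GLM would answer a question about microstructure and robot learning, while the prediction of functional gain would have no model in that trial's statistical section.

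**Working it through.** No figure is attached to this point, so the check is a comparison of sections. The sample sizes stand in the same statistical sections. They were checked only to confirm that this issue does not touch them, using n per group = 2(1.960 + 1.282)² × (SD/difference)².
- Infants: 21.02 × (5.9/7.2)² = 14.1, so 15, as stated. The t-based value is 15.14, so 16.
- Adults: 21.02 × (5/6)² = 14.6, so 15. The t-based value is 15.62, so 16, as stated.

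Both rest on AHA change and are independent of the GLM paragraphs.

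**Step 1: where bimanual SAT comes from.** Grand Challenge 3, Evaluation criteria, defines it. Subjects move a common pointer with two robotic handles round a circuit, train over three days, and are scored by a performance index built from velocity and error. The Introduction and HP1.2 assign the robot to the stroke trial.

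**Step 2: whether infants have it.** The infant battery listed above contains no robot, no circuit task, no speed-accuracy score and no learning curve. The behavioural term in the infant GLM therefore has no data, and neither does the curve modelling.

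**Step 3: each hypothesis against the stated models.**

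| Hypothesis | Outcome needed | Predictor needed | Model in the trial's own section | Grand Challenge 4 |
|---|---|---|---|---|
| HP2.2 | mid-term clinical change | change in microstructure | none usable | none |
| HP2.3 | functional gain | baseline microstructure | none usable | partly (HP4.3, HP4.5) |
| HP3.2 | mid-term clinical change | change in microstructure | partly, through MskL only | none |
| HP3.3 | functional gain | baseline microstructure | none | partly (HP4.3, HP4.5) |
| HP3.4 | functional gain | baseline MskL | none | none |

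HP3.2 is marked partly because the adult Evaluation criteria list robot-assessed bimanual MskL at the body-function level, so it is one of the clinical outcomes.

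**Step 4: whether the direction of the GLM rescues the adult model.** The text speaks of correlations between microstructure and MskL, so either could be the dependent variable. It makes no difference. With two variables, microstructure and MskL, no functional gain enters, and HP3.3 and HP3.4 both need one. In HP3.4 MskL is the predictor.

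**The case against.** The strongest reply has four parts.

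1. **The intended pairings are stated elsewhere.** The infant Evaluation criteria say the clinical assessments will be correlated with neuroplastic change. The Grand Challenge 3 hypotheses text says microstructural evolution will be set against mid-term clinical outcomes, and that baseline microstructure and MskL will be examined as predictors of functional gain. Model form is commonly left to a statistical analysis plan, which may exist. This stands as far as it goes: a missing model form alone would be no finding. But the infant section does state a model, and its outcome is not collected. A later plan would have to contradict the protocol text.

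2. **Grand Challenge 4 supplies analyses.** HP4.3 relates response to HABIT-ILE to baseline residual CST integrity in both populations. HP4.5 uses multiple regression of clinical response on CST, corpus callosum and whole-brain indices. This stands for much of HP2.3 and HP3.3. A reader might infer from the two GLM paragraphs that the brain-behaviour hypotheses are not tested at all; the documents do not support that. Grand Challenge 4 still offers no change-on-change model for HP2.2 and no MskL predictor for HP3.4. Its cross-population work is introduced as exploratory and seeks markers common to both groups. Grand Challenge 1 also aims to combine baseline imaging, clinical and biomechanical measures to predict recovery, but gives no model for MskL.

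3. **The adult GLM is a legitimate analysis.** Adults perform the task, and the paragraph does not claim to test HP3.2 to HP3.4. This stands. A reader might treat the two trials as sharing one fault, and they do not: in infants the variable is absent, while in adults the model is misaligned with the listed hypotheses.

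4. **The affected analyses are not the randomised comparisons.** This stands fully.

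**Conclusion.** The infant part is an error as written. The only association model in Grand Challenge 2's statistical section names a stroke-only robotic outcome, cannot be fitted, and does not match HP2.2 or HP2.3. It should be corrected before analysis. This rests on the infant assessment list being complete, and nothing in the document suggests that infants use the robot.

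The adult part is a lesser matter of alignment. The GLM can be fitted and touches HP3.2 in part, but it does not match HP3.3 or HP3.4. HP2.2 and HP3.4 are the two hypotheses for which the document gives no usable model anywhere.

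No numerical size can be given. A reader might want a false-positive rate for pooled correlations that omit arm. That would need the shift in an imaging index between arms, which the documents do not state. It would also apply only where both variables can move with treatment (HP2.2, HP3.2), since randomisation does not systematically shift baseline predictors. The comparisons of mini-AHA and ad-AHA between arms, and their sample sizes, are untouched.

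**What to change.** **Grand Challenge 2, Statistical analysis.** Replace the MskL outcome with change in mini-AHA, from T0 to T0+15 days and from T0 to T0+90 days, and delete the MskL curve modelling.

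**Grand Challenge 3, Statistical analysis.** Add models, or substitute them for the present GLM, with change in ad-AHA as outcome. The predictors are change in microstructure (HP3.2), baseline microstructure (HP3.3) and baseline MskL (HP3.4). The existing MskL model may stay if labelled as an additional analysis.

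**Handling of arm, both trials.**
- HP2.2 and HP3.2, where arms are pooled: AHA change = b0 + b1·arm + b2·microstructure change, with b2 the quantity of interest. The arm term keeps a treatment effect on both variables from appearing as an association between them.
- HP2.3, HP3.3 and HP3.4: AHA change = b0 + b1·arm + b2·baseline marker + b3·arm × baseline marker, with b3 the quantity of interest. Alternatively, restrict the analysis to HABIT-ILE-treated periods, including the control group's delayed training. A main effect of arm alone is not enough, because the stated question is what predicts gains induced by HABIT-ILE. The treated-only version cannot by itself separate prediction of response from general prognosis, and the text should say so if that option is chosen.

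**Cost.** One rewritten paragraph in each trial section. All the variables are already planned, and no sample size, visit or assessment changes.
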